## Prior and concomitant medication

All patients will receive the SoC of each site for COVID19. Additionally, they will receive the investigational treatment.

SoC medicines and supportive care is permitted according to institutional guidelines. All concomitant medications should be recorded, from the date the informed consent is signed until discharge of the patient.

**Criteria for Discontinuation of Study Treatment**

Subjects may voluntarily withdraw consent to participate in the study for any reason at any time. This will not cause a detriment in their treatment or clinical follow-up.

If a subject discontinues the study, the investigator will try to perform all the needed evaluations to ensure that no adverse event occurs.

## Study medication may be discontinued in the following instances:

- Discharge from the hospital/ institution.
- Concomitant illness that would, in the judgment of the investigator, affect assessments of clinical status to a significant degree.
- Toxicity, or toxicity that, in the judgment of the investigator, compromises the ability to continue study-specific procedures or is considered not to be in the subject’s best interest.
- Subject request to discontinue for any reason.
- Subject's non-compliance.
- Pregnancy during the study.

1. STUDY PROCEDURES AND ASSESSMENTS

The study procedures for each subject enrolled in the study are presented in tabular form in **Table 2** and described in the text that follows.

## Screening Visit

## Subjects will be screened within two days before randomization and dosing to determine eligibility for participation in the study.

- Obtain written informed consent.

After the informed consent is signed, the following assessments will be performed:

- Review SARS-CoV-2 testing.
- Focused medical history including the following information: demographics, date of first symptom, description of symptoms, allergies, concomitant medications and past medical history.
- Targeted physical examination including vital signs (heart rate, temperature, blood pressure), body weight, and height.
- Documentation of respiratory status:
- Respiratory Rate
- SpO2 at rest or PaO2
- Fraction of inspired oxygen (FIO2)
- Oxygen supplementation:
  - nasal cannula
  - high flow oxygen therapy
  - mask with a reservoir bag
  - non-invasive ventilation
- Radiographic findings (chest X ray or chest CT).
- Obtain blood samples if not done in the previous 48 hours for:
- Hematology and coagulation: Hematocrit, Hemoglobin, Mean Corpuscular Hemoglobin Concentration (MCHC), MCV (Mean Corpuscular Volume), Platelets, Red blood cells, White blood cells with differential (Basophils, Eosinophils, Lymphocytes, Monocytes, Neutrophils). **D-Dimer.**

# Chemistry: Glucose (fasting or non-fasting), Urea, Creatinine, Sodium, Potassium, Calcium, Chloride, Total Protein, Albumin, Bilirubin (total and direct), Aspartate Aminotransferase (AST), Alanine Aminotransferase (ALT), Lactate Dehydrogenase (LDH), Ferritin, C-reactive Protein (CRP) , troponin.

# Markers of Immunological function: Immunoglobulins, serum cytokines (IL-6, IL-1, TNFa, IFNb, IL-10); T cell repertoire: CD3 (CD4, CD8), naive CD45RA+CD27+, central memory CD45RA-CD27+, effector memory CD45RA-CD27- y EMRA CD45RA+CD27-, Activated T cells (HLADR+), T regs (CD4+CD25+CD127low), Tgd; NK cells repertoire CD56+CD3- (KIR (2DL1, 2DL2/3, 3DL1), NCR (NKp30, NKp44, NKp46), NKG2D); NKT cells, B cells, memory B cells (CD19+CD27+).

# Additional investigational studies: Blood samples will be stored for research use. These samples will be processed to obtain the cells and a phenotypic study will be carried out to see the recovery in time of immunological markers using the flow cytometry technique. The functionality of infected COVID-19 cells and recovered cells will be studied by co-culture assays to see cytokine secretion by flow cytometry. In addition, plasma cytokines will be studied by protein assays.

- Pregnancy test (for women of childbearing potential).
- Record any serious adverse events and all adverse events related to protocol-mandated procedures occurring after signing the consent form.

Study subjects who fulfil all the inclusion criteria and none of the exclusion criteria should be immediately randomized.

Randomization and dosing should occur on the same day if possible.

## Baseline/Day 0 Assessments

The following evaluations are to be completed at Day 0 visit (infusion date).

The investigator must have confirmed eligibility before proceeding to randomization on the Day 0 visit.

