## Donor selection criteria:

The blood donor selection will be done by the Regional Blood Transfusion Center with the following criteria:

1. Male or female patients ≤ 65 years
2. Subjects SARS-CoV-2+ tested by PCR+ during their disease
3. Complete resolution of symptoms at least 14 days prior to donation
4. Subjects must have at least one SARS-CoV-2 negative test by PCR from a nasopharyngeal swab, or, if available, a negative SARS-CoV-2 viremia tested by quantitative PCR in blood, before the blood donation.
5. Donors must have HLA typing and KIR typing performed, in order to decide treatment assignment for patients.
6. Subjects must be tested, at least, for the following:

[figure not shown]

* At least IgG, ideally IgG and IgM

** Mandatory for foreign patients, recommended for nationals

Blood donor apheresis will be split into 2 parts, NK cells (CD3-/CD56+) will be selected for Arm 1 and memory T cells (CD45RA-) for Arm 2.

Both blood products will be infused freshly whenever possible. If necessary, the product will be cryopreserved and frozen for future use.

Blood product from one donor can be utilized for more than one patient.

Donors and patients will be HLA tested. If one or more HLA class I match between donor and recipient is present, they will receive memory T cells. If donor and recipient have less than 1 HLA class I match or HLA-KIR mismatch, they will receive NK cells.

See Figure 3.

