******Figure 1. Schematic representation of procedure for blood donor obtention**

## Inclusion criteria

Patients eligible for inclusion in this study have to meet all of the following criteria:

- Male or female patients ≤ 80 years of age.
- Patient with diagnosis of COVID-19 infection with laboratory confirmation by reverse-transcription PCR (RT-PCR) of SARS-CoV-2 or other methods used according to each center protocol prior to study entry.
- Onset of symptoms < 12 days prior to administration of study treatment.
- **Phase I criteria:** Patients requiring hospitalization for COVID-19, with **pneumonia** diagnosed with chest radiograph or computed tomography imaging or **lymphopenia** (absolute lymphocyte counts below 1.2 x 10^9^cells /L) **AND** O_2_Sat ≤ 94% on room air at screening, no oxygen requirement or with an oxygen need of **≤ 2.5 lpm** in nasal cannula.
- **Phase II criteria:** Patients requiring hospitalization with **pneumonia** diagnosed with chest radiograph or computed tomography imaging or **lymphopenia** (absolute lymphocyte counts below 1.2 x 10^9^cells /L) **AND** O_2_Sat ≤ 94% on room air at screening, requiring or not oxygen supplementation (nasal cannula, oxygen mask with reservoir, non-invasive ventilation, etc), but **excluding** mechanical ventilation.
- Have a negative pregnancy test documented prior to enrollment (for females of childbearing potential).
- Be willing and able to comply with study procedures.
- Patients with the ability to comprehend and sign the informed consent
- Written informed consent obtained prior to any screening procedures.

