## Subject Treatment Assignment

Patients will be allocated into two groups: Arm A and Arm B depending on HLA typing.

For the phase I, patients on each arm will subsequently undergo a correlative allocation into the different cohorts (1,2,3).

The decision to proceed to each subsequent dose level (next cohort) will be made based on safety and tolerability data from the prior lower dose level. Safety data for at least 7 days post-dose from all the subjects at the prior lower dose will be reviewed before dose escalation.

The next cohort will open if all the patients in the previous cohort have been included and no safety issues have aroused during the follow-up after cell infusion (data of at least 7 days after cell infusion is required to proceed to each subsequent dose). Patients will continue to be followed for possible DLTs during the 21 days following cell infusion.

For phase II, eligible patients will be allocated to arm A or B considering HLA typing and within each arm they will then be randomized in a 1:1 ratio to 1 of 2 treatment groups (SoC or SoC+RP2D).

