## Secondary outcomes:

- Time (days) to normal level of lymphocytes.
- Proportion of patients showing clinical improvement at day 7 according to the investigator (based on respiratory status and blood-result tests).
- Proportion of patients receiving a second cycle.
- Time (days) to first negative SARS-CoV-2 PCR after infusing adoptive NK cells or adoptive memory T cells.
- The incidence of treatment-related adverse events (new or worsening from baseline) will be summarized by system organ class and/or preferred term, severity, type of adverse event and relation to study treatment. They will be defined by the Common Terminology Criteria for Adverse Events (CTCAE) Version 5.0
- Duration (days) of hospitalization.
- Time (days) to discharge or to a NEWS (Appendix 1) of ≤ 2 and maintained for 24 hours, whichever comes first.
- Time to improvement by one category on a 7-point ordinal scale (Appendix 2).
- Subject clinical status (on a 7-point ordinal scale) at day 14.
- Proportion of patients requiring intensive care unit.
- All-cause mortality at Day 28.

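### In Phase II, Day 0 is tied to the infusion date, which standard-of-care patients do not have, so an infusion later than randomisation would give the two groups different Day 14 windows

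*Protocol*

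**What the plan says.** The Baseline/Day 0 Assessments section of the protocol ties the start of the study clock to treatment: "The following evaluations are to be completed at Day 0 visit (infusion date". Its next sentence puts randomisation on that same visit: "The investigator must have confirmed eligibility before proceeding to randomization on the Day 0 visit".

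The end of the Screening Visit section loosens the link between the two events. It first says "Study subjects who fulfil all the inclusion criteria and none of the exclusion criteria should be immediately randomized", and then "Randomization and dosing should occur on the same day if possible". The opening of that section requires screening to fall no more than two days ahead of randomisation and dosing.

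In Phase II, patients are first allocated to an HLA arm. Under Subject Treatment Assignment, "within each arm they will then be randomized in a 1:1 ratio to 1 of 2 treatment groups (SoC or SoC+RP2D". One of the two groups therefore receives no infusion. The trial is open label and no sham infusion is described.

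The primary Phase II outcome is recovery through Day 14, compared by a chi-square test at day 14. Neither the outcome section nor the statistical analysis paragraph restates where the count begins. Two other items are anchored to treatment: the inclusion criterion "Onset of symptoms < 12 days prior to administration of study treatment" and the secondary outcome "Time (days) to first negative SARS-CoV-2 PCR after infusing adoptive NK cells or adoptive memory T cells".

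**The concern.** A randomised comparison needs one time origin that exists for every patient and is fixed at or before randomisation. Here the stated origin, the infusion date, exists for only one of the two Phase II groups. When infusion and randomisation fall on the same day, nothing is lost. When they do not, Day 0 has two meanings, and no rule says which applies.

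The natural reading would then count 14 days from infusion in the cell group and 14 days from randomisation in controls. Measured from randomisation, the cell group would have 14 days plus the lag in which to recover. In a one-sided superiority test this works in favour of the cells. A cell-group patient who is never infused would have no Day 0 at all, a problem that cannot arise in the same way for a control.

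Some delay is plausible, because the product is a selected fraction from a donor apheresis and "Both blood products will be infused freshly whenever possible".

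**Working it through.** **Inputs from the protocol.** One-sided alpha 0.05, power 0.80, recovery 45% on standard of care against 64.29% on cells, and 82 patients (Sample Size table, Study Population section). The 82 per HLA arm are split 1:1, which gives 82/2 = 41 per compared group.

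**Reproducing the plan's figure.** With the pooled one-sided formula, n = [1.645·√(2p̄(1−p̄)) + 0.842·√(p1(1−p1)+p2(1−p2))]² / (p2−p1)².
- p̄ = (0.45+0.6429)/2 = 0.5464 and p2−p1 = 0.1929.
- n = (1.158+0.581)²/0.0372 = 81.3, so 82. This matches the table.
- The 82 that the formula returns is a number per compared group. Results are therefore shown for both 41 and 82 per group.

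**Bound on the lag.** If randomisation and dosing both have to fall within two days of screening, and randomisation follows screening, the gap between them is at most about two days.

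**Assumptions, not in the protocol.** Constant daily recovery rate; no true effect; every cell patient delayed by d days; recoveries between randomisation and infusion counted as cell-group recoveries; controls counted from randomisation.

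**Spurious difference.** Cell-group recovery is q = 1 − (1−0.45)^((14+d)/14).
- d = 0: q = 0.450, difference 0.
- d = 1: q = 0.473, difference 2.3 points.
- d = 2: q = 0.495, difference 4.5 points.

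The planned difference is 64.29 − 45 = 19.29 points, so two days would supply 4.5/19.29 = 23% of it with no effect.

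**One-sided error.** Error = Φ[(q − 0.45 − 1.645·SE0)/SE1]. SE0 is the pooled and SE1 the unpooled standard error of the difference. For d = 2 and 82 per group, SE0 = 0.0780 and SE1 = 0.0779, so (0.045 − 0.1283)/0.0779 = −1.07 and Φ = 0.143.

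| Lag in every cell patient | Added recovery | Error, 41 per group | Error, 82 per group |
| --- | --- | --- | --- |
| 0 days | 0 | 5.0% | 5.0% |
| 1 day | 2.3 points | 7.5% | 8.9% |
| 2 days | 4.5 points | 10.8% | 14.3% |

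**Sensitivity to the control rate.** For a 2-day lag, the added recovery is 4.2 points at a 40% control rate and 4.7 points at 50%. The error is 10.4% and 11.1% with 41 per group, and 13.6% and 14.9% with 82 per group.

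**Sensitivity to the share delayed.** The bias is roughly proportional. If half the cell patients slip by two days, the added recovery is 0.5 × 4.5 = 2.25 points, close to the 1-day row. If a quarter slip by one day, it is 0.25 × 2.3 = 0.6 points.

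**Sensitivity to how early recoveries are handled.** If patients who recover before infusion are left out because they have no Day 0, a constant rate has no memory. Recovery within 14 days of infusion is then 45% among those infused, and the window bias vanishes. The problem becomes loss of patients from one randomised group. Losing early recoveries works against the cells, and losing those who worsen or die works for them.

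**The case against.** The strongest reply is that the protocol treats randomisation and infusion as one visit. Randomisation is placed on the Day 0 visit, same-day dosing is urged, and the Phase II schedule has a single Screening/D0 column. Controls therefore have a usable Day 0, their randomisation date, and the bias is nil whenever both events fall on one day. All of that stands. It does not say what happens when dosing slips, which the protocol permits.

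Delay may also be uncommon. Product may be frozen, one donor can serve several patients, donor selection starts early, and HLA allocation to an arm precedes randomisation. These points lower the likely frequency but do not remove the possibility. The protocol gives no figure for it.

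The time origin of an endpoint is often left to a statistical analysis plan. Here, however, the protocol itself fixes the anchor, and it fixes one that half of Phase II lacks.

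A reader might infer several stronger things that the text does not support:
- That lags of three days or more are in play. The screening rule, read literally, excludes them.
- That the protocol prescribes unequal windows. It does not; they arise only with a lag, and only on one reading of Day 14.
- That the symptom-onset criterion can never be checked in controls. With randomisation and dosing on one visit, it can be assessed that day. What is unclear is its meaning if dosing is later, and for a patient with no infusion.
- That time to PCR negativity is badly distorted. Sampling is on Days 7, 14, 21, 28 and 90 with a window of one day either way, so a lag of up to two days is small against that grid.

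**Conclusion.** The defect stands in a limited form. Day 0 is defined by an event that Phase II controls do not have, while dosing after the day of randomisation is allowed. If that happens, the Day 14 primary comparison can have unequal windows, and never-infused cell patients have no Day 0.

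The error rates in the table are an upper range, not an estimate. They require every cell patient to be delayed by the full lag, a constant recovery rate, and recoveries before infusion to be counted. A reader might add a further bias from patients lost before infusion to the same figures. The two should not be combined: the calculation needs those patients kept, and if they are dropped, the net direction is unknown.

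The change should be made, because it is simple and the possible bias falls on the primary outcome. The present wording does not show that the trial would be biased in practice.

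**What to change.** For Phase II, state that Day 0 is the date of randomisation in both groups. Apply it to the primary outcome, all time-to-event outcomes (including time to first negative PCR), Day 28 mortality and the visit schedule. Analyse all randomised patients from that date in the group to which they were assigned, including cell-group patients who are never infused.

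Keep days since infusion as a separate count for dose-limiting toxicity, chimerism and infusion-related safety only.

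Reconcile the symptom-onset criterion, which is counted from administration of study treatment, with the facts that eligibility is confirmed before randomisation and that controls receive no infusion.

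The cost is a wording amendment. The analysis needs both the randomisation date and the infusion date for each patient. It is reasonable to expect that both are captured, but the protocol does not say so, and the case report form should be checked.

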## Schedule of activities phase II

Table 3: Schedule of activities Phase II

| All the visits have a window of +/- 1 day | **Screening/D0** | **D1-D90 or until discharge** | **D7** | **D 14** | **D 21** | **D 28** | **D 90** |
| --- | --- | --- | --- | --- | --- | --- | --- |
| **Informed Consent** | x |  |  |  |  |  |  |
| **SARS-CoV-2 PCR testing** |  |  | x | x | x | x | x |
| **Medical history** | x |  |  |  |  |  |  |
| **Concomitant medications** | x | x | x | x | x | x | x |
| **Physical examination** | x | x | x | x | x | x | x |
| **Vital signs** | x | x | x | x | x | x | x |
| **Respiratory status** | x | x |  | x | x | x | x |
| **Hematology** | x | X^3^ (day 3) | x | x | x | x |  |
| **Biochemistry** | x | X^3^ (day 3) | x | x | x | x |  |
| **Markers of immunological function^1^** | x |  | x | x | x | x | x |
| **Blood sample for additional investigational studies** | x | X (day 3) | x | x | x | x |  |
| **Donor chimerism** |  | X^2^ (day 3) | x | X^2^ | X^2^ | X^2^ |  |
| **Pregnancy test** | x |  |  |  |  |  |  |
| **Scales (NEWS and 7 point scale)** | x | x | x | x | x | x | x |
| **Evaluation of patient recovery** |  |  |  | x |  |  |  |
| **Improvement according to investigator/Second dose^**^** |  |  | x |  |  |  |  |
| **Adverse events** | x | | | | | | |

^1^ Performed at screening and weekly. Please review section 7 for specific assessments.

^2^ Day: 3 and 7. If donor chimerism persists by day 7, repeat on days 14, 21, 28 and then continue weekly (until disappearance). Stop once it is negative.

^3^Day 3

^**^ Those patients showing clinical improvement at day 7 according to the investigator (based on respiratory status and blood-result tests) who have not shown previous toxicities of grade 3 or higher **and** if donor chimerism doesn´t persist, can receive a second cycle with the same dose at Day 7, if the investigator considers it appropriate.

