**Phase II**

The primary outcome in Phase II in this study is:

- The incidence of patient recovery infusing adoptive NK cells or adoptive memory T cells.
- **Recovery is defined as:** Proportion of participants in each group with normalization of fever and oxygen saturation [criteria for normalization: temperature < 38°C armpit, and SpO2 > 94%, sustained for at least 24 hours] or lymphopenia recovery **through Day 14.**

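### Phase II has no common Day 0: it is tied both to infusion, which standard-of-care patients never have, and to randomisation, so late infusion can shift the Day 14 window in the cell group only

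*Protocol*

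**What the plan says.** Under Baseline/Day 0 Assessments the protocol states: "The following evaluations are to be completed at Day 0 visit (infusion date". Two lines on, the same section states: "The investigator must have confirmed eligibility before proceeding to randomization on the Day 0 visit". So one visit carries two definitions, the date of infusion and the date of randomisation.

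Other sections bear on whether these dates agree:

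- The end of the screening section says "Study subjects who fulfil all the inclusion criteria and none of the exclusion criteria should be immediately randomized", followed by "Randomization and dosing should occur on the same day if possible". No maximum gap is given there.
- The Screening Visit section opens with "Subjects will be screened within two days before randomization and dosing to determine eligibility for participation in the study".
- Subject Treatment Assignment says that Phase II patients are placed in Arm A or B by HLA typing and then randomised 1:1 within the arm to SoC alone or SoC plus cells. The SoC group has no infusion, and no section gives it a separate Day 0.
- The Phase II primary outcome is "The incidence of patient recovery infusing adoptive NK cells or adoptive memory T cells", with recovery assessed up to Day 14. The day from which those 14 days run is not stated.
- One secondary outcome is written from infusion: "Time (days) to first negative SARS-CoV-2 PCR after infusing adoptive NK cells or adoptive memory T cells". The other secondary outcomes state no infusion origin.

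**The concern.** A randomised comparison needs follow-up to start at the same point in both groups. Here the only definition of Day 0 refers first to an event that half of the Phase II patients never have. If a cell patient is infused k days after randomisation and Day 14 is counted from infusion, that patient has 14 + k days from randomisation in which to recover. An SoC patient, dated from the randomisation visit, has 14.

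Two gaps follow directly from the text. A patient randomised to cells but never infused has no Day 0, hence no Day 14, and could drop out of the comparison. Time to first negative PCR has no starting point in the SoC group.

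The trial is open label, so a Day 0 improvised for SoC patients would be set by people who know the allocation. At stake is a Phase II primary result tilted towards the cells by the way days are counted.

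**Working it through.** **1. The planned figure.** The sample-size table gives 82 for SoC recovery P1 = 45% and intervention recovery P2 = 64.29%, with one-sided alpha 0.05 and power 0.80. With the pooled-variance formula, p̄ = (0.45 + 0.6429)/2 = 0.546 and d = 0.193:

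n = [1.645·√(2p̄(1 − p̄)) + 0.842·√(P1(1 − P1) + P2(1 − P2))]² / d² = (1.158 + 0.581)² / 0.0372 ≈ 81.4, rounded up to 82 per randomised group.

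The figure reproduces and is not disputed here. It fixes the inputs: 45% SoC recovery and a planned effect of 19.3 points. As the allocation is written, 82 per HLA arm split 1:1 gives 41 v 41. Results for 82 v 82 are shown as well.

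**2. Assumptions, none of which the protocol supplies.** No true treatment effect; constant recovery hazard; every cell patient infused d days after randomisation; Day 14 counted from infusion in the cell group and from randomisation in SoC; recoveries between randomisation and infusion count.

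**3. Recovery in the cell group.** The hazard is h = −ln(0.55)/14 = 0.0427 per day. Recovery is 1 − exp(−(14 + d)h):

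- d = 1: 1 − exp(−15h) = 47.3%, a gain of 2.3 points
- d = 2: 1 − exp(−16h) = 49.5%, a gain of 4.5 points, or 4.5/19.3 = 23% of the planned effect

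For SoC recovery between 40% and 50%, the gain is 2.2 to 2.4 points at d = 1 and 4.2 to 4.7 points at d = 2.

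**4. False-positive rate of the one-sided 5% test.** With n per group and q the cell-group recovery, the rate is Φ{[(q − 0.45) − 1.645·√(2p̄(1 − p̄)/n)] / √([0.45·0.55 + q(1 − q)]/n)}, where p̄ is now (0.45 + q)/2.

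| Delay in every cell patient | 41 v 41 | 82 v 82 |
| --- | --- | --- |
| 0 days | 5.0% | 5.0% |
| 1 day | 7.5% | 8.9% |
| 2 days | 10.8% | 14.3% |

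**5. If only some infusions are late.** The gain shrinks in proportion. With a quarter of cell patients delayed by 2 days it is 0.25 × 4.5 = 1.1 points, and the rejection rate at 41 v 41 is about 6%.

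**6. If recoveries in the gap do not count.** Under a constant hazard, patients not yet recovered at infusion have 45% recovery over the next 14 days, the same as SoC, and the gain disappears. The protocol does not say how such recoveries are handled.

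**7. With one origin.** If both groups are counted from randomisation, d = 0, the artificial difference is zero and the error rate returns to 5%.

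**The case against.** The best defence is that the plan intends no gap. Eligible patients are to be randomised at once, dosing is to follow the same day where possible, and randomisation is placed at the Day 0 visit. Where that is done, the two definitions coincide, the randomisation visit serves as Day 0 for SoC, and no bias arises. The Day 0 section also serves Phase I, where every patient is infused. This stands, and it makes the concern conditional. It does not remove it, because same-day dosing is a wish with no stated limit and the text does not say which date governs when the two differ.

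A uniform 2-day delay is also an extreme. On a plain reading of the screening window, it needs randomisation on the day of screening and infusion at the limit, in every patient. That stands too: the figures above are upper values for each delay.

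Some stronger readings are tempting but not supported:

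- A reader might infer that every time outcome starts later in the cell group. Only time to negative PCR is written from infusion. The Day 14 outcome and the other time outcomes state no origin, and duration of hospitalisation does not depend on Day 0.
- A reader might infer that mortality is biased towards the cells. If all randomised patients count and Day 28 runs from infusion, the cell group has longer in which to die, which works against it. The bias favours the cells only if deaths before infusion are dropped, and nothing in the protocol says so.
- A reader might add the Table 3 rule, "All the visits have a window of +/- 1 day", as a further source of bias. It applies to both groups alike, and the handling of visit windows is commonly left to the analysis plan.

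**Conclusion.** The point holds in conditional form. The protocol gives Day 0 two meanings, leaves SoC patients without a stated Day 0 in Phase II, and allows infusion to fall after randomisation. For cell patients infused late, the Day 14 window can then run longer from randomisation than in SoC, which favours the cells on the primary outcome provided that recoveries in the gap count. Never-infused cell patients have no Day 14, and time to negative PCR is undefined for SoC.

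The primary-outcome gain is 2.3 points for a 1-day and 4.5 points for a 2-day delay in all cell patients, with one-sided error of 7.5% and 10.8% at 41 v 41. This rests on an assumed constant hazard, 45% SoC recovery and no true effect. Neither the length nor the frequency of delay is in the protocol, so the actual bias may be much smaller, or nil if all dosing is same-day. The direction for mortality is open.

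This is more than missing detail, because the protocol does fix an origin and fixes it on an event that only one group has. It should be fixed.

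**What to change.** For Phase II, define Day 0 as the date of randomisation in both groups for recovery up to Day 14, the 7-point scale, Day 28 mortality and the time-to outcomes. Count all randomised patients from that date, including cell patients never infused. Keep the infusion date as origin only for infusion-specific measures such as donor chimerism, and for DLT timing in Phase I.

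The text to amend is the Baseline/Day 0 Assessments section, the Phase II primary outcome (stating that its 14 days run from randomisation) and the secondary outcomes (removing infusion as the start for time to negative PCR). The Day 7 second-cycle visit is a treatment rule on which this point takes no position; the amended text should only make clear which date it is counted from.

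The cost is wording, with no change in sample size. The case report form is not shown, so the team should confirm that it captures both dates. The one drawback is that late-infused patients will have slightly less than 14 days after infusion by Day 14, which is mildly conservative for the cells.
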